|                                        | 
patients with <math>\geq 1</math> graft with a significant (50-99%) stenosis at 1-year post-CABG angiography, compared to those who received placebo.
 
ii. The incidence of the composite of non-fatal MI (using new definition), all-cause mortality, and repeat revascularization (redo CABG or PCI) perioperatively and at 1 year is lower in the fish oil versus placebo group of patients.
 
Tertiary Outcome
 
Surgical Arm: The two groups will be compared with respect to the incidence of the composite endpoint of perioperative and 1-year non-fatal MI (using old definition), all-cause mortality, repeat revascularization (redo CABG or PCI) (major adverse cardiac events, MACE) and stroke.
 
Pharmacological Arm: The two groups will be compared with respect to the incidence of the composite endpoint of perioperative and 1-year non-fatal and fatal MI (using old definition), death, repeat revascularization (redo CABG or PCI) (major adverse cardiac events, MACE) and stroke.
 |
| Statistical Considerations             | 
Intention to treat analysis
 
Comparison of the proportion of patients developing the primary outcome at 1-year using Pearson chi-square test.
 
Overall type 1 error rate at 5%
                                                                                                                                                                                                                                                                                                                                                                                                                                                                                                                                                                                                                                                                                                                                                                                                                                                                   |

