### **3.3 Method of treatment allocation**

Prior to the trial, all surgeons will be provided with a copy of the trial protocol. Research personnel will screen patients in the preoperative assessment clinic to identify patients who fulfill the eligibility criteria. The personnel will also review the daily surgical list for eligible in-patients. Patients who fulfill the eligibility criteria will be approached for informed consent. Eligible and consenting patients will be randomized by calling a 24 hour interactive voice response system (IVRS) or by logging-in to a web-based randomization service. Treatment allocation to either “no touch” or conventional SVG harvesting, and fish-oil supplementation or placebo will be performed according to a computer generated randomization list. This will be stratified by site using a factorial design; blocked randomization will be performed with randomly sized blocks to maintain concealment. Randomization will also be stratified according to the control technique (open vs. endoscopic) to minimize bias following the pilot phase. Patients will be considered as randomized as soon as the treatment allocation is given over the telephone.

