## **5 STUDY PROCEDURES**

### **5.1 Treatments**

#### **A. SURGICAL ARM**

Eligible patients undergoing multi-vessel CABG with ≥1 SVG, will have the study SVG directed to the most important coronary target intended for a venous conduit. **In the experimental arm**, patients will be randomized to have the study SVG harvested from their lower leg using the novel, pedicled, atraumatic **“no touch” technique** (45-48). **In the control group**, patients will have their study SVG graft harvested in a **conventional fashion** without a pedicle.

The atraumatic “no touch” approach involves a longitudinal incision in the lower leg below the knee to the medial malleolus. However, the SVG is harvested with its surrounding tissue (pedicled). It is not manually dilated; it is left *in situ* until required and allowed to dilate when exposed to arterial pressure. All study patients will undergo duplex scanning and mapping of the saphenous veins preoperatively, to assess the quality of the vein as well as limit the creation of flaps during the vein dissection. Saphenous veins will be harvested from the thigh in the event that the lower leg vein is of poor quality or small size, or in patients with marked edema or peripheral vascular disease with concerns regarding wound healing.

The conventional approach involves a longitudinal incision in the lower leg, just below the knee to the medial malleolus. The vein is identified and the adventitial layer is stripped to directly expose and visualize the SV and its branches. Vein from the thigh may be harvested for similar reasons as

discussed above. It is then excised and distended using heparinized saline. It is standard practice in many institutions to harvest SV using an endoscopic, minimally invasive rather than an open approach, for reasons of improved cosmesis and because local wound complications are reduced (70). For relevance and to reflect contemporary trends in practice, the control group/conventional approach may include the minimally harvested SVG, which is otherwise prepared in a similar manner, i.e. stripped of adventitia and manually distended, albeit through a smaller incision. A recent observational study of a large multi-centre sample (50) and post hoc secondary analysis from the large multi-centre PREVENT IV RCT (5) reported poorer patency and clinical outcomes using endoscopically harvested SVG, however, institutions that predominantly employ endoscopic harvesting may continue to choose this technique.

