### 5.4 Encouraging compliance

Noncompliance is not expected to be a major issue in this trial. The interventions are simple and the surgical intervention occurs at a single time-point and is controlled by the treating physician,

outcomes are objective, and data-forms are concise. Patient compliance to the study supplements will be monitored at follow-up visits via pill counts.

Patients are generally followed by their surgeons/cardiologists for several years after their procedure, and it is expected 99.9% follow-up at one month and over 99% follow-up at 6 months will be obtained. PHRI has substantial experience in documenting vital status in >99.5% in its clinical trials involving over 200,000 subjects recruited from over 50 countries and followed for up to 8 years. This expectation will be met in this study, especially with a post-surgical population in whom clinical follow-up by the surgeon for a minimum of 3 months is generally routine.

The overall study has been designed such that only one SVG is required to facilitate recruitment. We did consider restricting the study to patients who required at least 2 SVGs, as the event rates would presumably be greater. The chosen protocol does allow patients who are having only 2 grafts constructed (ITA and 1 SVG) and is compatible with patients undergoing more extensive arterial revascularization. We anticipate that the average number of vein grafts/patient will be 1.5 (as in GRIIP) (6). We considered restricting the control group to open harvesting rather than allow for endoscopic harvesting to be performed as well. We thought it important to include endoscopic harvesting as it is a commonly used technique, and there is recent evidence that endoscopic vein harvesting purports worse patency and clinical outcomes than conventional SVG harvesting (50). Although endoscopic patients will usually be unblinded, endpoint adjudication is blinded. Our post-hoc analysis will also aim to elucidate any difference in graft patency in the control SVGs harvested in the conventional open versus endoscopic techniques. We expect that the RRR will be similar or greater comparing endoscopic and no-touch versus open control and no-touch.

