### **8.3 Statistical Methods**

The primary comparison for the 2 main study questions (“no touch” vs. conventional SVG harvesting [primary endpoint: study SVG occlusion]; fish oil supplementation vs. placebo [primary endpoint: proportion of patients with >1 graft occluded]) will be performed using a Chi-square test according to the intention-to-treat principle. A test for interaction will be tested similarly and with logistic regression. Statistical significance is assumed for  $p < 0.05$ . The secondary graft occlusion endpoints, graft stenosis, or graft occlusion or significant stenosis, will also be tested with Chi-square or Fisher’s tests where appropriate, considering graft stenosis as a dichotomous variable, as well as logistic regression treating graft stenosis as an ordinal variable. Additional modeling will be performed post hoc with logistic regression, generalized estimating equation and bootstrapping techniques, to evaluate covariates of graft occlusion (7,18,71). Variables of interest in addition to the usual demographic factors include: open vs. endoscopic vein harvesting, serum lipid values; study centre; surgeon; time period of patient entry (to address a possible learning effect); timing of postoperative angiography; parameters related to the distal coronary artery target such as, size, quality, and factors related to the specific coronary artery grafted including the severity of the proximal stenosis. Other categorical outcomes (major cardiac events and vein harvest site complications) will also be compared with either Chi-square or Fisher’s Exact test where appropriate. The harvest site infection scores will be tested using t tests.

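### Randomization is stratified by site and control technique, but the primary test is an unstratified chi-square and no randomized contrast by technique is named: a minor, nearly free improvement

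*Protocol*

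**What the plan says.** On allocation, section 3.3 first fixes site: "This will be stratified by site using a factorial design; blocked randomization will be performed with randomly sized blocks to maintain concealment". It then adds the second factor: "Randomization will also be stratified according to the control technique (open vs. endoscopic) to minimize bias following the pilot phase".

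On the primary analysis, section 8.3 states for both factorial questions that the comparison "will be performed using a Chi-square test according to the intention-to-treat principle". The synopsis (Statistical Considerations) agrees: "Comparison of the proportion of patients developing the primary outcome at 1-year using Pearson chi-square test". Neither place mentions strata.

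The two stratification factors reappear in section 8.3 only under exploratory modelling: "Additional modeling will be performed post hoc with logistic regression, generalized estimating equation and bootstrapping techniques, to evaluate covariates of graft occlusion". The listed variables include "open vs. endoscopic vein harvesting, serum lipid values; study centre; surgeon".

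On technique, section 5.1 (Surgical Arm) leaves the control method to the centre: "institutions that predominantly employ endoscopic harvesting may continue to choose this technique". Section 5.4 plans a post hoc look at "any difference in graft patency in the control SVGs harvested in the conventional open versus endoscopic techniques". In the next sentence it states an expectation about the treatment effect: that the relative risk reduction of no-touch against endoscopic controls will be no smaller than against open controls.

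**The concern.** Two things do not line up.

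First, the analysis does not follow the design. When randomization is blocked within strata and event rates differ between strata, the treatment difference varies less than an unstratified test assumes. The test is then slightly conservative, and some precision bought by the design goes unused.

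Second, the expectation in section 5.4 concerns how the treatment effect varies with control technique, but the analysis named beside it compares two kinds of control graft with each other. Institutions choose the technique, so that comparison is observational and entangled with centre. The design offers something better. To stratify on control technique, the intended technique must be known at randomization for patients in both arms. Post-pilot patients therefore supply a randomized no-touch versus control comparison within each intended-technique stratum. If the trial is positive, readers will ask whether no-touch improves on open harvesting, on endoscopic harvesting, or on both. The protocol names no randomized analysis that answers this.

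**Working it through.** **1. The plan's own figures.** Section 8.5 gives 20% versus 14%, two-sided alpha 0.05 and 80% power. The usual unstratified formula is

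n = [z(α/2)·√(2p̄q̄) + z(β)·√(p1q1 + p2q2)]² / (p1 − p2)².

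With p̄ = 0.17: 2p̄q̄ = 0.2822 and p1q1 + p2q2 = 0.1600 + 0.1204 = 0.2804. Then n = [1.960 × 0.5312 + 0.8416 × 0.5295]² / 0.06² = 1.4868² / 0.0036 = 614.1, so **615**, as stated. The same formula gives 540 for 30% versus 22.5%. Power at 615 for the fish-oil question is 84.9%, and 615/0.80 = 769. All four match section 8.5. The sample size thus rests on an unstratified comparison.

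**2. Direction and rough size of the effect on type I error.** With near-equal allocation in each site, the null variance of the treatment difference depends on the average of p_s(1 − p_s) over sites. That average equals p̄(1 − p̄) − Var(p_s). The crude test uses p̄(1 − p̄), which is too large. To first order, Var(p_s) ≈ [p̄(1 − p̄)]²·SD², where SD is the between-site SD on the logit scale. The variance ratio is therefore about 1 − p̄(1 − p̄)·SD². At p̄ = 0.20 and SD = 0.5 (an assumption) this is 1 − 0.16 × 0.25 = 0.96. The effective critical value becomes 1.960/√0.96 = 2.00, and the type I error about 4.6%. The error can only fall below 5%, not rise above it.

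**3. Simulation.** Layout: 50 sites (section 8.5) with 25 evaluable patients each, or 1,250 in all, close to 1,550 × 0.80 = 1,240. Allocation is near-balanced within site, and half of the sites are endoscopic. There were 6,000 replicates per setting. The documents give neither the between-site SD nor the odds ratio of occlusion for endoscopic versus open sites. Both are assumed, over 0 to 1.0 and 1.0 to 1.5. CMH is the Cochran-Mantel-Haenszel test. Each cell shows the results for odds ratios 1.0 / 1.5.

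| Site SD | Type I, crude (%) | Type I, CMH by site (%) | Power, crude (%) | Power, CMH by site (%) |
|---|---|---|---|---|
| 0 | 5.5 / 4.8 | 5.4 / 4.9 | 81.3 / 80.3 | 81.1 / 80.4 |
| 0.3 | 4.7 / 4.5 | 4.8 / 4.8 | 80.8 / 80.4 | 81.1 / 80.8 |
| 0.5 | 4.3 / 4.9 | 4.7 / 5.3 | 81.9 / 81.0 | 82.8 / 81.9 |
| 0.8 | 4.0 / 4.1 | 4.7 / 5.0 | 81.9 / 80.6 | 83.4 / 82.2 |
| 1.0 | 3.9 / 4.0 | 5.1 / 5.0 | 82.2 / 83.0 | 84.5 / 85.0 |

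Simulation error is about 0.3 points for type I error and 0.5 points for power. Stratifying by technique alone moved power by about 0.2 points or less in every setting. A second set of 4,000 replicates on the same 50 × 25 layout gave crude power 81.4, 81.2, 81.3 and 81.9% against 81.2, 81.7, 81.9 and 84.3% stratified by site, at SD 0, 0.3, 0.5 and 0.8. The largest gap there is 2.4 points.

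**4. The technique question, side by side.** Section 5.4 predicts an effect by control type, which is a treatment-by-technique statement. The analysis it names is open versus endoscopic within controls. The interaction test in section 8.3 follows directly on the two factorial questions and names no technique stratum. So the predicted quantity and the named analysis differ, and only the first can be estimated from a randomized comparison.

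**5. What a within-stratum contrast can show.** Assume half of the evaluable patients fall in each technique stratum, so 615/2 ≈ 307 per group, with 20% versus 14% in both. Then z = [0.06 − 1.960 × √(0.2822/307)] / √(0.2804/307) = (0.06 − 0.0594)/0.0302 ≈ 0.02, and power is about 51%. An unequal split lowers it in the smaller stratum.

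**The case against.** The case for leaving the text alone is respectable. A chi-square after 1:1 blocked randomization within site is a valid test, and it matches the formula behind 615 and 540. The efficiency gain depends on a between-site SD that the documents do not give, and it is nil when that SD is 0. Section 5.4 openly labels the open versus endoscopic comparison as post hoc. Nothing forbids a within-stratum analysis, and subgroup and adjustment details are often left to a statistical analysis plan, which is not at hand. The remedy is also not purely a matter of wording, because technique stratification starts only after the pilot while pilot patients are pooled into the final analysis.

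Much of this stands, and it sets the size of the point. It does not remove the point: the protocol is not silent on the primary test but fixes it, twice, without the strata it randomizes on. It also states an expectation by technique and names only a non-randomized analysis beside it.

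Two stronger inferences about technique are tempting and not supported:

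- *The chosen analysis biases the open versus endoscopic comparison.* That comparison is confounded because institutions choose the technique. It would be so under any test, stratified or not.
- *The post hoc models will distort the treatment effect by adjusting for the technique actually received.* The arithmetic behind this worry is sound. No-touch grafts are not endoscopic, so with that coding the treatment term becomes no-touch versus open controls. Suppose half the controls are endoscopic, occlusion is 16% open and 24% endoscopic (mean 20%), and no-touch is 14%. The randomized odds ratio is (0.14/0.86)/(0.20/0.80) = 0.65, and the adjusted one (0.14/0.86)/(0.16/0.84) = 0.85. But section 8.3 does not say that the variable is coded as received, and it gives the models' purpose as evaluating covariates, not re-estimating treatment. This is a reason to state the coding, not an error in the plan.

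**Conclusion.** The point holds as a minor mismatch between design and analysis. A reader might infer that the primary test is invalid or that the stratification is wasted. Neither follows: the crude chi-square is unbiased, its type I error stays at about 4 to 5%, and stratified allocation still delivers balance. The cost is about 0 to 2 points of power at 20% versus 14%, over an assumed between-site SD of 0 to 1.0 with equal-sized sites, and almost all of it comes from site.

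The technique half matters more for interpretation than for power. The protocol anticipates an effect by control technique and has a randomized basis for estimating it, but names only the observational comparison. Naming the randomized contrast beforehand protects it from looking data-driven later. With about 51% power per stratum under an even split, it would describe consistency of effect rather than settle the question.

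**What to change.** 1. In section 8.3 and the synopsis, make the primary test a Mantel-Haenszel test or a logistic regression that accounts for site (small sites pooled, or a random site intercept) and intended control technique. The unadjusted chi-square can stay as a supporting analysis. The 615 per group need not change, since the site-stratified test had equal or higher power in every setting, within simulation error.
2. Pre-specify no-touch versus control within each intended-technique stratum, with a treatment-by-stratum interaction test.
3. State that technique enters these analyses as intended at randomization, not as received.
4. Keep the open versus endoscopic comparison among controls, labelled exploratory and non-randomized.

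Cost: free to cheap. Sparse sites need a pooling rule written before unblinding. The 50 pilot patients (50/1,550 = 3.2% of the total) were not stratified by technique and need an assignment rule, such as the usual practice of their site. The within-stratum contrasts will have limited power and should be reported as such.

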## **2 STUDY OBJECTIVES**

The objective of the pilot phase of the study is to determine the number of eligible patients of the total isolated CABG patients, the consent rate, adherence to the protocol including rate of follow-up cardiac CT angiography, medication discontinuation and the overall incidence of the primary outcome. Achieving a recruitment rate of 1-2 patients/centre/month will determine if the study will proceed to the full phase III trial.

The primary objective of this study for the **Surgical Arm** is to determine whether a novel atraumatic (“no touch”) technique of pedicled saphenous vein graft (SVG) harvesting results in a lower **proportion of study SVGs** that are totally (100%) occluded on 1-year post-CABG angiography and death due to cardiovascular or unknown causes, compared to conventional SVG harvesting techniques, in patients undergoing CABG.

The primary objective of this study for the **Pharmacological Arm** is to determine whether N-3 polyunsaturated fatty acid (fish oil) oral supplementation results in a lower **proportion of patients** with  $\geq 1$  graft (study SVG, non-study SVG or arterial graft) totally (100%) occluded at 1-year post-CABG angiography and death due to cardiovascular or unknown causes, compared to those who received placebo.

The secondary objectives for the **Surgical Arm** are to determine whether:

- i. The “no touch” technique of SVG harvesting results in a lower ***proportion of study SVGs*** that have a significant stenosis (50-99%) on 1-year post-CABG angiography compared to conventional SVG harvesting techniques.
- ii. The incidence and severity of adverse SVG harvesting events at 1-year post-CABG (infection, haematoma, swelling, neuropathy, quality of life measures) are similar between the “no touch” and conventional groups of patients.
- iii. The incidence of the composite of non-fatal myocardial infarction (MI) (using new definition, see Section 5.5), all-cause mortality, and repeat revascularization (redo CABG or percutaneous coronary intervention [PCI]) perioperatively and at 1 year is lower in the “no touch” versus conventional group of patients.

The secondary objectives for the **Pharmacological Arm** are to determine whether:

- iii. Fish oil supplementation results in a lower ***proportion of patients*** with  $\geq 1$  graft with a significant (50-99%) stenosis at 1-year post-CABG angiography, compared to those who received placebo.

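### Harvest-site harm is compared with a control group that mixes open and endoscopic harvest, so the pooled difference moves with the site mix and describes neither kind of site

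*Protocol*

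**What the plan says.** - **Objective.** Surgical secondary objective ii in section 2 concerns "The incidence and severity of adverse SVG harvesting events at 1-year post-CABG" and asks whether they are alike in the no-touch and conventional groups. It lists infection, haematoma, swelling, neuropathy and quality of life.
- **Control group.** Section 5.1 A states that "the control group/conventional approach may include the minimally harvested SVG" and that "institutions that predominantly employ endoscopic harvesting may continue to choose this technique". No target share or cap is set. It explains the use of endoscopic harvest as "for reasons of improved cosmesis and because local wound complications are reduced (70". The no-touch technique is described there with a longitudinal lower-leg incision.
- **Test.** Section 8.3: "Other categorical outcomes (major cardiac events and vein harvest site complications) will also be compared with either Chi-square" or, where suitable, Fisher's exact test. For severity: "The harvest site infection scores will be tested using t tests". Neither sentence mentions control technique.
- **Allocation.** Section 3.3: "Randomization will also be stratified according to the control technique (open vs. endoscopic) to minimize bias following the pilot phase".
- **Where open versus endoscopic is analysed.** Section 5.4 plans a post-hoc look at graft patency among control grafts, and section 8.3 lists the technique as a covariate of graft occlusion. Both concern graft outcomes. No analysis of leg harm by control technique is stated.

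**The concern.** The protocol says that its two control techniques differ on local wound complications, then compares no-touch with the two combined. The resulting difference is a weighted average of two contrasts, no-touch against open and no-touch against endoscopic. The weight is the share of patients at endoscopic-control sites, which the institutions determine and the design does not fix.

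Two trials with the same true harm at each kind of site could therefore report different pooled differences. A surgeon at an endoscopic site would read a figure that is too small for that site's patients, and a surgeon at an open site one that is too large. The protocol plans to look at graft outcomes by control technique. It states no such look at leg harm, the outcome on which it says endoscopic harvest is better.

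**Working it through.** **Check of the formula.** The documents give no figure for harvest-site harm. The power formula used below (two proportions, pooled variance, no continuity correction, two-sided 0.05) reproduces the plan's surgical sample size: 20% versus 14% at 80% power gives 615 per group, and 615 / 0.80 = 769, both as in section 8.5.

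**Inputs from the protocol.** 1,550 patients equally allocated give 1,550 / 2 = 775 per surgical group. I assume that all contribute harm data. The direction p_endo < p_open comes from section 5.1.

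**Inputs assumed.** The complication rates, the endoscopic share w, and a no-touch rate that is alike at both kinds of site.

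**Algebra.**
- Pooled control rate = (1-w) p_open + w p_endo
- Pooled excess = p_NT - [(1-w) p_open + w p_endo]
- Endoscopic-site excess minus pooled excess = (1-w)(p_open - p_endo)
- Pooled excess minus open-site excess = w(p_open - p_endo)

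Both gaps are positive whenever 0 < w < 1 and p_open > p_endo. The direction needs no assumed rate, only the like no-touch rate.

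**Illustrations.** Scenario A: no-touch 12%, open 10%, endoscopic 4%, so the excess is 2 points at open-control sites and 8 at endoscopic-control sites. Scenario B: 10%, 10% and 5%, so 0 and 5 points. The endoscopic stratum has 775w patients per group.

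| Scenario | w | Pooled excess (points) | Power, pooled test | Power, endoscopic stratum | Power, treatment-by-stratum test |
|---|---|---|---|---|---|
| A | 30% | 12 - 8.2 = 3.8 | 70% | 89% | 48% |
| A | 50% | 12 - 7.0 = 5.0 | 92% | 98% | 53% |
| A | 70% | 12 - 5.8 = 6.2 | 99% | over 99% | 44% |
| B | 30% | 10 - 8.5 = 1.5 | 17% | 53% | 38% |
| B | 50% | 10 - 7.5 = 2.5 | 41% | 75% | 42% |
| B | 70% | 10 - 6.5 = 3.5 | 71% | 88% | 34% |

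The last column divides the difference between the two stratum risk differences by its standard error. For A at w = 50%, with 387.5 per group and stratum, the standard error is √[(0.1056 + 0.0900 + 0.1056 + 0.0384) / 387.5] = 0.0296. Then z = 0.06 / 0.0296 = 2.03, and power is Φ(2.03 - 1.96) = 0.53.

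**Precision, A at w = 50%.** The half-widths of the 95% intervals are:
- pooled: 1.96 √[(0.1056 + 0.0651) / 775] = 2.9 points
- endoscopic stratum: 1.96 √[(0.1056 + 0.0384) / 387.5] = 3.8 points
- open stratum: 1.96 √[(0.1056 + 0.0900) / 387.5] = 4.4 points

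Power in the open stratum for 12% versus 10% is 14%.

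**The case against.** **The pooled contrast answers the stated question.** Objective ii compares no-touch with conventional harvest, and section 5.1 deliberately defines conventional to include both techniques; section 5.4 records that an open-only control was considered and not chosen. This stands. A reader might infer that the pooled test is biased or invalid. It is not: allocation is randomised within site and, after the pilot, by control technique, so the test is sound for the average over the enrolled mix. The difficulty is what that average means for either kind of site.

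**Stratum tables belong in a SAP.** Partly fair. The protocol does not exclude them, and a SAP that is not shown may contain them. But the protocol is not silent here: it names an unstratified test for this outcome and mentions control technique only for graft outcomes. Section 5.4 also expects the multi-centre design to reveal any influence of endoscopic harvesting on outcomes, but it specifies no harm analysis that would do so.

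**The size is assumed.** This stands. It is also tempting to say that the protocol predicts little excess over open harvest. It does not. Section 5.1 supports only fewer local wound complications with endoscopic than with open harvest, and says nothing of an equal advantage for swelling, haematoma or neuropathy.

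**A missed excess is not inevitable, and the strata are not always well powered.** Both parts stand. In scenario A the pooled test has 92% to 99% power at shares of 50% to 70%. The 98% power in the endoscopic stratum is one favourable cell; for 10% versus 5% it is 53% to 88% over shares of 30% to 70%. In scenario B, however, the pooled test has only 17% to 71%, less than the endoscopic stratum at each share.

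**Reading a non-significant result as similarity is a separate problem.** Agreed. It arises because no margin is set, and stratifying does not cure it.

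**Conclusion.** The point holds as one of interpretation and reporting, not of validity. The pooled comparison estimates the average harm over whatever mix is enrolled. Given the protocol's own statement about endoscopic wound complications, and a no-touch rate that is alike across sites, this average lies below the excess at endoscopic-control sites and above that at open-control sites.

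The size cannot be derived from the documents. Under the assumed rates and shares of 30% to 70%, the pooled figure falls short of the endoscopic-site excess by 1.8 to 4.2 points in scenario A (8 - 6.2 and 8 - 3.8) and by 1.5 to 3.5 points in scenario B (5 - 3.5 and 5 - 1.5). The primary patency comparison is outside this point. The change is worth making because a factor already used in the randomisation resolves most of the ambiguity at little cost.

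**What to change.** In section 8.3:
- Keep the pooled no-touch versus conventional comparison for objective ii, but stratify it by control technique, for example by Mantel-Haenszel. This respects the randomisation; the summary remains an average over the mix.
- Pre-specify risk differences with 95% confidence intervals for harvest-site complications within the open-control and endoscopic-control strata. The comparator in each is the no-touch patients of the same stratum.
- Assign the 50 pilot patients, who enter the final analysis under section 8.5 but precede this stratification under section 3.3, by their site's declared technique.
- Treat any treatment-by-stratum test as descriptive. Its power is about 34% to 53% under the assumed rates, so a non-significant result would not show that harm is alike in the two strata.

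Cost: a few sentences and two extra table columns, with no additional patients. The downside is precision: stratum intervals are wider than the pooled one (3.8 and 4.4 points against 2.9 in scenario A at an even split), and the open stratum has little power for small differences.
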